### Interventions

#### Active—Morning Bright Light Therapy (MBLT)

Participants randomized to receive MBLT were shipped a light box (LightPad, Aurora Light Solutions, Las Vegas, NV, USA) to be received following the end of their baseline period, as we have previously published [25]. Participants were instructed on how to operate the LightPad, which involved plugging it in and pressing the “on” button. However, the lux received depends on the distance participants sit from the light source and thus, participants were instructed to sit no less than 24 inches away to ensure exposure to 10,000 lux of non-UV light. This was the maximum illuminance/range in commercially available units, and the recommended illuminance for white light to promote synchronization of circadian sleep-wake cycles in humans [29]. Participants were instructed to obtain their light exposure within 120 minutes of waking. Thus, participants were allowed 60 minutes of flexibility in their morning routine before MBLT, while still receiving 60 minutes of bright light within the advised post-wake window. Detailed instructions, including visual aids, were provided to promote compliance (e.g., positioning the light box at a 45° angle relative to their face), noting that instructions for light therapy had previously been shown to be significant moderators of efficacy [52]. Participants were also encouraged to concurrently engage in other normal activities of daily living during this time (e.g., read a newspaper, work on a computer, eat breakfast).

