To our knowledge, the field of sleep medicine is without a fully powered, sham-controlled, masked, randomized controlled trial establishing feasibility, acceptability and efficacy of MBLT to improve sleep quality in Veterans with mTBI. Furthermore, to our knowledge, a fully remote randomized controlled trial device intervention protocol has not yet been successfully implemented in Veterans with mTBI–a challenging population not only due to significant participant disability/burden, but also due to the logistical and regulatory challenges of device management and electronic data capture behind the Veterans Affairs (VA) firewall. We sought to fill both gaps by implementing LION (Light vs Ion therapy), whose protocol is described herein. This trial proposed to acquire complete data in n = 120 Veterans allocated 2:1, active-intervention (MBLT, n = 80) versus sham-intervention (deactivated ion therapy, n = 40). MBLT delivered white light (10,000 lux at the eye), whereas the negative ion generator was fully deactivated, but modified to appear “on”, i.e., via installation of a small fan to generate a quiet, whirring sound, as well as a small LED status light. This sham-intervention was modeled from prior work by Lam et al., [28] in which bright light or sham-intervention therapy was compared to fluoxetine for the treatment of depression. Participants in both groups engaged with devices to the same extent (i.e., over 60 minutes within 2 hours after waking) throughout the 28-day intervention period, with the same degree of expectancy and study team interaction. The brand of the light box was chosen due to being commercially available, in use for decades (including within the VA), and previously validated for illuminance metrics and spectral power density [25]. Dose, timing, and duration were all established from prior work investigating the effect of MBLT for the treatment of insomnia, circadian entrainment, and seasonal affective disorder [46–48].

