#### Fidelity adherence monitoring

Adherence to both MBLT and sham was tracked and consistently monitored in several ways. First, we called participants at the onset of initiating their intervention, as well as weekly thereafter to address any questions and promote their adherence by way of addressing any challenges they had encountered. Second, participants manually recorded their engagement with their device (time and duration) as part of their daily sleep-diary. Third, we utilized a combination of actigraphy and luxometer data (generated and collected by the Actiwatch-2 as well as a HOBO Pendant MX Temperature/Light Data Logger affixed to the LightPad) to objectively track MBLT adherence. Luxometer data via the HOBO and/or actiwatch provided evidence of device usage, and activity counts via the actiwatch provided an estimate of movement such that the combination of low activity counts (i.e., suggesting being sedentary) and evidence for device usage, suggested protocol adherence. This did not preclude the possibility that participants turn the LightPad on and either have it incorrectly placed (facing away from them), or simply remain sedentary in a different room, but the combination of these metrics provided a best approximation while minimizing participant burden.

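### The seating rule for the light box sets only a minimum distance, which can cap the 10,000 lux dose but cannot secure it

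*Protocol article*

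**What the plan says.** The Introduction of the protocol article states the dose in the active arm: "MBLT delivered white light (10,000 lux at the eye", delivered over 60 minutes within two hours of waking for 28 days. It adds that the light box was "previously validated for illuminance metrics and spectral power density".

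The section Active—Morning Bright Light Therapy (MBLT) gives the rule meant to achieve that dose. It first notes that "the lux received depends on the distance participants sit from the light source". It concludes from this that "participants were instructed to sit no less than 24 inches away to ensure exposure to 10,000 lux of non-UV light". Of the 10,000 lux figure it then says "This was the maximum illuminance/range in commercially available units", and it describes the same figure as the recommended level for white light.

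The same section mentions detailed instructions with visual aids, and names a 45° angle of the box to the face as one example. The article gives no maximum distance and no fixed distance anywhere.

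**The concern.** The stated purpose of the rule is to make sure that the dose is reached. A lower limit on distance works against excess dose, not against too little. The limit that protects against too little light is an upper one, and that is the one absent from the sentence.

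Light is the active ingredient here, and it is taken at home without supervision while the participant reads, works or eats. The article itself says that "instructions for light therapy had previously been shown to be significant moderators of efficacy", so the wording of the positioning rule is not incidental.

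What is at stake depends on what participants were told:

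- If they were given the rule as printed, some could comply fully and still receive less than the intended dose. The trial would then test a lower and more variable exposure than the one named.
- If they were given a correct working distance, the trial is sound on this point, and the article misstates the dosing rule for anyone who reuses it.

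**Working it through.** The article gives no lux-by-distance figure to reproduce, so the check is one of direction.

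**Inputs**

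- Permitted seating distance d under the printed rule: d ≥ 24 inches, with no upper limit (section on MBLT).
- Intended dose: 10,000 lux (section on MBLT), at the eye (Introduction).
- Distance c at which the box gives exactly 10,000 lux: not stated, so left free.
- Premise: for a given box, illuminance falls as d rises. The article says that lux depends on distance. The direction is ordinary physics and does not depend on any particular fall-off law.

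**Step 1.** Under that premise, a seat receives at least 10,000 lux only if d ≤ c.

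**Step 2.** Compare the seats that the rule permits (d ≥ 24) with the seats that reach the dose (d ≤ c):

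| Distance c | Permitted seats that reach 10,000 lux | Permitted seats that fall short |
|---|---|---|
| below 24 in | none | all |
| exactly 24 in | only d = 24 in | every d > 24 in |
| above 24 in | 24 in ≤ d ≤ c | every d > c |

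**Step 3.** The last column is never empty. The rule has no upper limit, so seats beyond c are always permitted and always receive less than 10,000 lux. In none of the three cases does the rule do what the sentence says it does.

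**Step 4.** Reverse the limit. If the rule were d ≤ c, every permitted seat would receive at least 10,000 lux. A safety minimum m below c could be kept alongside it, giving m ≤ d ≤ c. Both purposes are then served.

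**How many could still benefit.** The Results count 104 participants as complete and 12 as randomized and ongoing. That is 104 + 12 = 116, against a target of 120 complete. How many of the 12 had already finished their 28 days of exposure is not stated, so the number still to be treated cannot be fixed from the article.

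**The case against.** The strongest reply has three parts.

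First, this is probably a slip of wording, not the rule in use. The participant instructions and visual aids are not shown, and a journal article condenses such detail. That stands: the point concerns the printed rule, and nothing shows that any participant was dosed under it. It does not remove the point, because the article does not merely omit the working distance. It states a specific rule and gives it a purpose that the rule cannot serve.

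Second, a minimum distance is sensible if 10,000 lux is a target, since sitting closer would exceed it. That also stands, and it is why the rule is best called one-sided. A bare maximum would leave the opposite gap. A target still needs an upper limit on distance, or a fixed distance.

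Third, the Introduction reports earlier validation of the box's illuminance. That supports the device. The distance and position used for the validation are in a source not shown, so it can neither repair the printed rule nor be dismissed.

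A reader might go further and fault the adherence monitoring for not measuring light at the eye. The documents do not support making that a finding. The section Fidelity adherence monitoring says openly that "This did not preclude the possibility that participants turn the LightPad on and either have it incorrectly placed", calls its measures a best approximation, and describes a call at the start and weekly calls after it. The Statistical analyses section plans regressions on Actiwatch lux within the MBLT arm.

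**Conclusion.** The point holds as one about the stated dosing rule. A minimum of 24 inches with no maximum does not ensure 10,000 lux, so as written it does not secure the dose at the eye given in the Introduction. The conclusion rests only on illuminance falling with distance, and not on any calibration of the box.

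Two stronger readings are tempting, and the documents support neither:

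- *That participants were under-dosed.* Actual distances are not reported. One could assume 10,000 lux at 24 inches and a seat at 36 inches, and compute 10,000 × (24/36)² = 4,444 lux under an inverse-square law or 10,000 × (24/36) = 6,667 lux under an inverse-distance law. Both the calibration distance and the seat are invented for that sum, so it is no evidence of a shortfall in this trial.
- *That 10,000 lux is unsupported as the tested dose whatever participants were told.* If the sentence is a slip and the instructions gave the correct distance, the intended dose in the Introduction can stand.

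The consequence is limited. The intention-to-treat comparison of the randomized arms is unaffected. What could change is the description of the dose to which the estimate applies. It is worth correcting because it governs the active ingredient and costs almost nothing.

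**What to change.** 1. Check the participant instructions and visual aids against the device's specified working distance.
2. Restate the rule in the MBLT section as *at* or *no more than* that distance, and keep any safety minimum beside it.
3. Only if participants were given the one-sided limit: correct the instruction for anyone still to be treated, disclose that earlier participants received it, and describe 10,000 lux in the Introduction and the MBLT section as the nominal output at the working distance.

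The cost is a check of existing materials and one corrected sentence, plus, in the conditional case, a corrected instruction, a disclosure and a qualifier on the dose. The dose statement may then read slightly less favourably. Sample size and primary analysis do not change.

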#### Sham—Deactivated negative ion generator

The sham intervention consisted of a no-light, negative ion generator (SphereOne, Inc.) of comparable size and electricity demands to the LightPad, also shipped to participants at the end of their baseline period. All negative ion generator devices were modified to emit an audible quiet hum with a green status light, and deactivated to not emit ions, as previously published [28], which falsely indicated being in an active state. The sham arm followed identical timing and duration as described above for the active-MBLT arm. Therefore, participants in the sham arm also received the same degree of subject-investigator interaction and instructions for device adherence.

#### Fidelity adherence monitoring

Adherence to both MBLT and sham was tracked and consistently monitored in several ways. First, we called participants at the onset of initiating their intervention, as well as weekly thereafter to address any questions and promote their adherence by way of addressing any challenges they had encountered. Second, participants manually recorded their engagement with their device (time and duration) as part of their daily sleep-diary. Third, we utilized a combination of actigraphy and luxometer data (generated and collected by the Actiwatch-2 as well as a HOBO Pendant MX Temperature/Light Data Logger affixed to the LightPad) to objectively track MBLT adherence. Luxometer data via the HOBO and/or actiwatch provided evidence of device usage, and activity counts via the actiwatch provided an estimate of movement such that the combination of low activity counts (i.e., suggesting being sedentary) and evidence for device usage, suggested protocol adherence. This did not preclude the possibility that participants turn the LightPad on and either have it incorrectly placed (facing away from them), or simply remain sedentary in a different room, but the combination of these metrics provided a best approximation while minimizing participant burden.

### Outcomes

#### Primary

LION’s primary outcome was designated as an improvement in sleep following MBLT compared to sham. This was accomplished via several means, though self-reported sleep disturbances via the Insomnia Severity Index (ISI) remained primary [53]. The ISI is a 7-item measure, each item a 5-point Likert scale (0–4) with a total score range of 0–28 where higher scores indicate worse sleep [54,55].

#### Self-report, actigraphy, and sleep diary

Potential changes in sleep were further evaluated via other validated self-report measures (e.g., Epworth Sleepiness Scale, ESS [56]; Functional Outcomes of Sleep Questionnaire-10, FOSQ-10 [57]; and the Sleep Hygiene Index, SHI [58]), and objective metrics derived from participants’ sleep diary and wrist-based actigraphy (Philips Respironics, Bend, OR, USA). Philips Actigraphy devices use a solid-state, piezoelectric, monoaxial accelerometer to measure activity and silicon photodiodes to measure photopic light (5–100,000 lux; 400–900 nm), with data sampled at 32 Hz and aggregated into 2-minute bins. Philips Actiware (v 6.3.0) was used to process and analyze these data relying first on the automated algorithmic detection of rest-active periods, with further refinement based on *a priori* defined outcomes collected in the sleep diary. For example, participants were queried whether their sleep was unusually disrupted (ranging from being ill to falling asleep or being awoken at unusual times due to things outside of their control), and if so, this 24-hour period was excluded from analysis. Participants were directed to wear the watch on their non-dominant wrist and to keep clothing from covering the light sensor as much as possible. Daily sleep diaries were collected using the TWILIO^™^ platform, which directly integrated with our HIPAA-compliant secure REDCap database. Participants were prompted in the morning via Short Message Service (SMS) text format. The first prompt was at 8:00 AM in participants local time, with reminders sent at 10:00 AM and 12:00 PM if no response had been entered. If participants did not respond within that 24-hour period, earlier prompts expired ensuring all data is collected within 24 hours. Sleep diary metrics included self-reported time in bed/asleep, time out of bed/awake, number of awakenings during the night, and (during the intervention period) device usage.

The primary comparison across timepoints was pre- vs post-intervention. Only self-reported sleep symptoms were evaluated at the follow-up time point as daily diaries and actigraphy were not continued during the follow-up period.

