Light therapy, generally administered in the morning (i.e., morning bright light therapy; MBLT) is cost-effective, low-burden, home-based, and non-pharmacologic. Our recent single-arm, open-label clinical pilot study demonstrated preliminary feasibility and limited efficacy for MBLT to improve sleep, as measured both by self-report and objective actigraphy-based measures in Veterans with mTBI [25]. Much of the precedence for this pilot study stemmed from a large body of work associating mTBI with subsequent effects on sleep quality, mood and daytime alertness [26–39]. Additional rigorous studies have been executed comparing the effects of blue spectrum light with a placebo control amber light on sleep in individuals with mTBI, and found improvement in subjective daytime sleepiness, although objective measures of sleep via actigraphy were unchanged [40–42]. Two other recent studies examined light therapy on daytime fatigue in individuals with TBI (including severe TBI) [43,44]. Additionally, light therapy was also recently shown to improve post-traumatic stress disorder (PTSD) symptom severity in Veterans with PTSD, albeit without a change in self-reported or actigraphic metrics of sleep quality [45].

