## Discussion

The LION protocol was designed as a sham-controlled, participant-masked randomized controlled trial evaluating effectiveness of MBLT to improve self-reported and objective aspects of sleep quality, with subsequent potential “downstream” effects evaluated in neurobehavioral function, cognition, mood, and quality of life, and blood/sweat based-biomarkers of inflammation in Veterans with mTBI. This project was sponsored by MTBI^2^ and is entering its final year of enrollment and data analysis. At the time of this interim analysis for feasibility and acceptability, we have completed data collection in ~80% (n = 104) of the proposed target sample (*n* = 120).

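### Sleep-diary variables are called objective although the same section defines them as self-reported; reserve the label for actigraphy and add one actigraphy run without diary input

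*Protocol article*

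**What the plan says.** The protocol article, under Outcomes (Self-report, actigraphy, and sleep diary), names two groups of sleep measures beyond the ISI. The first is validated questionnaires: the Epworth Sleepiness Scale, the FOSQ-10 and the Sleep Hygiene Index. The second is "objective metrics derived from participants’ sleep diary and wrist-based actigraphy".

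Later in that section the diary's content is given: "Sleep diary metrics included self-reported time in bed/asleep, time out of bed/awake, number of awakenings during the night", plus device use during the intervention period. On capture it says: "Participants were prompted in the morning via Short Message Service (SMS) text format". The section closes by again setting diaries apart from self-report: "Only self-reported sleep symptoms were evaluated at the follow-up time point as daily diaries and actigraphy were not continued during the follow-up period".

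The diary has a second role. Actiware first detects rest and active periods automatically, with "further refinement based on *a priori* defined outcomes collected in the sleep diary". The example given is that a participant who reports unusually disrupted sleep has that 24-hour period left out of the analysis.

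The Abstract lists actigraphy, self-report and diary entries as primary sleep outcomes. The Discussion states the aim as testing whether light therapy can "improve self-reported and objective aspects of sleep quality".

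**The concern.** A diary that the participant fills in each morning is self-report, open to the same recall and expectancy effects as the ISI. Placing it with actigraphy under an objective label blurs a distinction that the trial itself draws when it states its efficacy aim.

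The distinction could matter here. The Introduction describes trials of blue against amber light in mild traumatic brain injury in which subjective daytime sleepiness improved, "although objective measures of sleep via actigraphy were unchanged". A similar split in this trial, with the diary moving and actigraphy flat, is a plausible result. Under the present wording an author could call that split an objective improvement and cite the protocol in support.

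A related point concerns actigraphy. If diary answers shape the rest intervals and decide which days are dropped, the actigraphy result is not wholly independent of what participants report.

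**Working it through.** No arithmetic applies. The label enters no formula for sample size, power or alpha. The check is to set the places where the article classes the diary, or uses the word objective, side by side.

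1. **Label.** Outcomes, Self-report, actigraphy, and sleep diary: the diary is on the objective side, separate from the questionnaires.
2. **Content.** Same section: "Sleep diary metrics included self-reported time in bed/asleep, time out of bed/awake", and number of awakenings. No instrument records these; the participant answers a text message. Items 1 and 2 cannot both hold.
3. **Closing sentence of that section.** Self-reported symptoms continue to follow-up; diaries and actigraphy do not. The diary again falls outside self-report, so item 1 is not a single slip.
4. **Use of the term elsewhere.** The Introduction ties objective sleep measurement to actigraphy. Under Fidelity adherence monitoring, device use is entered by hand in this same diary, while the light logger and Actiwatch provide the objective tracking. Table 3 then reports self-reported use and an objective estimate on separate rows. One diary is thus self-report for adherence and objective for sleep.
5. **What the label touches in the analysis.** Statistical analyses fits a mixed model for each outcome. No composite is formed, and no rule lets any one of several objective measures establish a result. The sample size paragraph (under Overview and ethics) and the Primary outcome section put the ISI first, and the ISI is correctly called self-reported. Moving the diary to the self-report class therefore changes no model, error rate or power.
6. **What the label touches in reporting.** The Discussion splits efficacy into self-reported and objective sleep. The label decides on which side a diary effect is counted. With a diary effect and null actigraphy, the present label permits a claim on both sides; the corrected label permits it on the self-reported side only.
7. **Diary input to actigraphy.** Participants are randomised after the 2-week baseline, so any exclusion of a 24-hour period during the 28-day intervention follows randomisation and depends on participant report. For comparisons with other outcomes, Statistical analyses averages actigraphy over 3 to 5 consecutive nights from about the last 7 days of each period. If night 4 of 7 is dropped, two runs of 3 nights remain and no run of 4 or 5 is possible. A single diary answer can therefore change which nights are averaged. The article gives no count of excluded periods, so the size of this effect is unknown.

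**The case against.** The strongest reply is that this is loose wording with no analytic consequence. The section heading, the Abstract and Table 3 all list diary and actigraphy separately, the diary items are openly described as self-reported, and each outcome has its own model. A diary-only effect would be visible as exactly that. The Results call actigraphy and diary supplemental to the ISI. All of this stands, and it is why the point is minor.

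A second reply is that the phrase may mean actigraphy metrics scored with diary help, since the description of Actiware scoring follows soon after. This does not clear the text. The section goes on to list diary metrics in their own right, and the Abstract makes diary entries an outcome.

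A third reply is that expectancy bias needs a difference between arms, and the design works to prevent one: all participants are told that half of the devices in each arm are inactive, and instructions and contact are the same. That is fair. Masking by deception, with investigators aware that the sham is inactive, does not show that masking fails. The point does not need it to fail; it needs only that self-report is called self-report.

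The prior evidence is also mixed. The Introduction says that the team's own pilot showed preliminary improvement on both self-report and actigraphy, so a split result is possible rather than expected.

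**Conclusion.** The classification is wrong on the article's own terms and should be corrected. It is a minor correction: no estimate, alpha, power or sample size changes. What changes is the claim that a diary-only effect may support.

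Two stronger readings are tempting and do not hold. A reader might infer that the label would reverse the trial's conclusion on objective sleep. The documents contain no composite and no decision rule that would do so, and the separate actigraphy result would still be reported. A reader might also infer that the label governs a headline outcome, because the Abstract counts the diary among the primary measures. The ISI leads, the trial is powered on it, and the Results treat the diary as supplemental.

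The sensitivity analysis rests on a narrower fact: participant answers given after randomisation can remove actigraphy days. Whether this alters the actigraphy result cannot be judged from the article.

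**What to change.** - In the outcomes section, and wherever the analysis plan repeats it, class all diary variables as self-report and reserve objective for actigraphy.
- State that any conclusion on objective sleep rests on actigraphy alone, and that a diary effect without an actigraphy effect is reported as self-reported improvement.
- Add one actigraphy sensitivity analysis using the automated Actiware rest intervals, with no diary refinement and no diary-based exclusion of 24-hour periods. Keep the diary-refined scoring for the main analysis.

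The first two changes are wording, apart from a narrower claim if only the diary moves. The third needs a small amount of re-scoring of data already collected. Its scoring will be somewhat noisier, because unrefined intervals and disrupted nights stay in, so it should be read as a check and not as a replacement. The Results say that outcomes have not yet been analysed formally, so the change can be made before efficacy results are known.
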